## Abstract

**Background:**

People with alcohol use disorders often exhibit an “alcohol approach bias”, the automatically triggered action tendency to approach alcohol. Approach bias is likely to persist following withdrawal from alcohol, and contribute to the high rate of relapse following withdrawal treatment. Cognitive bias modification (CBM) training has been shown to attenuate approach biases and lead to reduced relapse rates. However, no large multisite trial of CBM specifically within a residential withdrawal treatment setting has previously been conducted. This study aims to test whether CBM delivered during residential withdrawal treatment leads to reduced relapse rates and reduced use of acute health services following discharge, and to test possible moderators of CBM’s effect on alcohol use.

**Methods:**

Three hundred alcohol-dependent inpatients are being recruited from three withdrawal treatment units in the Melbourne metropolitan area. Participants complete baseline measures of alcohol approach bias and cue-evoked desire for alcohol, followed by four daily sessions of computerised CBM training (or sham training if randomised to the control group). Approach bias and cue-evoked desire are re-assessed following the fourth training session. Follow-up assessments administered 2 weeks and 3, 6, and 12 months following discharge from the withdrawal treatment unit compare abstinence rates and acute and emergency healthcare service use between conditions. Pre-admission and follow-up substance use is derived from the timeline follow-back method, and approach bias towards alcohol with a computerised Approach Avoidance Task.

**Discussion:**

This study is the first multisite randomised controlled trial of cognitive bias modification delivered during acute alcohol withdrawal treatment. Withdrawal is theoretically an ideal period to deliver neurocognitive interventions due to heightened neuroplasticity and cognitive recovery. If effective, the low cost and easy implementation of CBM training means it could be widely used as a standard part of alcohol withdrawal treatment to improve treatment outcomes. Moderation analyses may help better determine whether certain subgroups of patients are most likely to benefit from it and therefore should be prioritised for CBM during alcohol withdrawal treatment.

**Trial Registration:**

Version 4 of the protocol (dated 1 August 2017) is registered with the Australian New Zealand Clinical Trials Registry, ACTRN12617001241325. Registered on 25 August 2017 (retrospectively registered).

## Background

Alcohol is one of the world’s most harmful drugs [1], responsible for 3.6% of deaths globally and 4.5% of the global burden of disease [2]. Alcohol consumption is a causal contributor to eight different cancers, numerous cardiovascular disorders (including hypertension, haemorrhagic stroke, and atrial fibrillation), pancreatitis, several liver diseases (notably cirrhosis and alcoholic hepatitis) and diabetes [3]. Excessive use can cause severe structural and functional neural abnormalities and result in significant cognitive dysfunction [4–6].

In Australia, alcohol is the most widely used drug, aside from caffeine. Despite recent evidence that people are drinking alcohol less frequently and more are choosing to abstain in recent years, many Australians continue to drink heavily and experience alcohol-related harm [7, 8]. Statistics indicate that more than one fifth of Australians meet lifetime *Diagnostic and Statistical Manual of Mental Disorders, Fourth Edition* (DSM-IV) criteria for an alcohol use disorder (AUD) [9]. Standard treatment for severe alcohol dependence in Australia often involves costly, intensive inpatient withdrawal treatment to manage acute withdrawal symptoms, followed by outpatient counselling and/or alcohol pharmacotherapy. Approximately 90% of patients relapse after withdrawal treatment, many within days of discharge, preventing successful engagement with post-withdrawal treatment and necessitating further episodes of inpatient withdrawal treatment [10]. Repeated readmission to withdrawal treatment, combined with this patient group's high rate of acute health service use, puts a high burden on the healthcare system. Novel interventions that reduce the proportion of patients who relapse have the potential to deliver cost savings to health and social welfare systems, and benefit alcohol-dependent individuals’ health and wellbeing, as well as their families.

Contemporary models of addiction frame AUD as (at least partially) the result of faulty information processing systems [6, 11–13]. With chronic use, neuroadaptations in the striatum and limbic system (i.e. the “reward pathways”) drive automatic, impulsive, reward-seeking behaviour and induce sensitisation to alcohol and alcohol-related stimuli. This results in cognitive biases, including ‘attentional bias’, which is the tendency for alcohol cues to disproportionately capture attention, and ‘approach bias’, which is the tendency for alcohol cues to induce automatic approach actions [11, 14]. As individuals become more dependent on alcohol, these cognitive biases increasingly direct thought and behaviour towards alcohol cues in the environment, and it is suggested that the frontal-striatal executive system becomes less capable of moderating or suppressing the actions driven by the overactive striatal-limbic system. Some research has found that these cognitive biases positively predict hazardous drinking [15, 16], although these findings have not always been consistently replicated [17]. Some studies suggest that this relationship between cognitive bias and problematic drinking is moderated by personality traits, particularly impulsivity, although there are conflicting findings regarding whether impulsivity is related to stronger or weaker relationships between cognitive bias and drinking [18–20].

Cognitive biases are typically measured using computerised tasks involving responses (e.g. using a keyboard, joystick, or mouse) to motivationally relevant and neutral images [16]. Differences in reaction times when responding to motivational stimuli, relative to neutral stimuli, indicate cognitive bias. Cognitive biases can be modified by adapted ‘training’ versions of these measurement tasks, known as Cognitive Bias Modification (CBM) training [21, 22]. Early CBM centred on anxious and phobic patients, re-training them to focus on positive or neutral cues, rather than cues associated with threat or distress, and these techniques have since been successfully adapted for treatment of AUD [23].

In the alcohol Approach Avoidance Task (AAT), respondents are presented with both alcohol-related and non-alcohol-related images and asked to respond with either an approach or avoidance behaviour to an arbitrary component of the presentation (such as the orientation or framing of the image), using a joystick or another similarly interactive medium [24]. For example, the approach behaviour typically involves respondents pulling the joystick towards themselves, which increases the size of the image, approximating the physical experience of approaching the stimuli. Likewise, the avoidance behaviour typically involves pushing the joystick away, which reduces the size of the image, giving the appearance that it is ‘receding’ into the ‘distance’. Training involves pushing alcohol-related images away the majority of the time (e.g. typically 90–100%), so that respondents repeatedly practice an avoidance action that counters their bias to automatically approach these stimuli, thereby theoretically weakening the approach bias [22].

The first CBM program that specifically targeted alcohol approach bias in a clinical population involved four consecutive daily sessions of alcohol AAT training to alcohol-dependent inpatients who had recently (at least 3 weeks prior) completed clinically supervised withdrawal from alcohol [25]. At pre-test, all participants demonstrated a strong approach bias towards alcohol. At post-test, participants in the experimental treatment arm demonstrated an avoidance bias towards alcohol, whereas controls (including two groups: one who were ‘trained’ with a control version of the task that involved avoiding only 50% of the alcohol-related images, and approaching the other 50%; another who did not do any training at all) maintained their initial approach bias. Participants who received CBM also reported lower rates of relapse (defined as 3 or more consecutive days of drinking; 46%) than controls (59%) at follow-up 1 year after treatment discharge. In two large subsequent studies, it was found that 6 or 12 sessions of CBM training delivered later in the post-withdrawal inpatient program was also associated with improved rates of abstinence, although the effect size was slightly reduced relative to the earlier study (8.5% less relapse) [26, 27]. Subsequent functional magnetic resonance imaging (fMRI) studies have shown reduced activation in both the medial prefrontal cortex and the amygdala in response to alcohol cue presentation after training, which correlated with measured changes in approach bias [28, 29]. This suggests that CBM reduces cue-evoked brain activity in regions involved in motivational salience, which may explain the increased rates of abstinence observed after training.

Since these initial reports of the efficacy of CBM, additional studies have been published, allowing for systematic reviews and meta-analyses on the effectiveness of CBM. The first of these [30] cast scepticism on its effectiveness. However, this review conflated studies of attentional bias modification, approach bias modification, and modification of other types of cognitive biases; included multiple addiction populations (i.e. alcohol and tobacco); and included studies of both clinical and non-clinical (non-dependent) participants. The validity of the review’s conclusion has recently been challenged on the basis that CBM has differential effects in relation to study type (laboratory experiments with student populations versus randomised controlled trials [RCTs] in clinical populations), mode of delivery (in person in controlled conditions versus via internet) and population (treatment-seekers versus those not seeking to change their behaviour) [31]. The authors also note that in clinical settings in RCTs with alcohol-dependent patients, approach bias has modest but significant effects as an adjunct approach when delivered alongside other psychosocial interventions such as cognitive behavioural therapy. A recent systematic review focused specifically on approach bias modification studies for alcohol use, tobacco use, or unhealthy eating which included behavioural outcome measures concluded that it confers positive effects, in terms of reduced consumption and increased rates of abstinence [32].

During alcohol withdrawal, the brain undergoes extensive structural and functional recovery and reorganisation. Significant increases in the grey matter of the insular and anterior cingulate cortices have been detected within the first 2 weeks of withdrawal [33]. These areas are involved with interoceptive sensitivity and cognitive control and are integral to the operations of the reward and executive systems [34]. These structural repairs are thought to underlie improvements in cognitive functioning during and after withdrawal [35, 36] and are indicative of a period of heightened neuroplasticity that, if harnessed through cognitive training, may facilitate the amelioration of maladaptive cognitive biases.

For these reasons, we previously conducted a pilot study of four sessions of CBM delivered during inpatient alcohol withdrawal treatment [37]. This study of 83 patients found a near-significant increase in rates of abstinence during the first 2 weeks following discharge from the withdrawal unit, relative to a sham-training condition, and this effect was significant when analysis was restricted to those participants who completed all four sessions of training. We focused on outcomes during the first 2 weeks following discharge because this is a crucial time for commencing engagement in ongoing post-withdrawal treatment, which often fails to occur due to rapid relapse. However, this study was not adequately powered, particularly for examining abstinence rates at later follow-ups, and the control condition did not involve exposure to alcohol images, which may have confounded findings (due to potential exposure effects).

Aside from this small pilot study, previous studies of CBM in alcohol-dependent samples have waited until several weeks after withdrawal to commence training. The efficacy of CBM during withdrawal treatment has therefore not yet been tested in any large, multisite trials. The present study is thus the first large study of CBM in a residential withdrawal treatment setting. This will also allow analyses exploring the moderating effects of clinical and personality traits, particularly approach bias, impulsivity, cravings, and severity of dependence, to help further elucidate the mechanisms governing CBM’s efficacy and which specific types of patients are likely to benefit most from it. Moreover, it overcomes an important limitation of the previous pilot study by ensuring that participants in the control condition have equal exposure to the same images as those used in the CBM condition.

## Methods

### Aims

The primary objective is to determine the efficacy of CBM training, compared to sham training, in a population undergoing inpatient withdrawal treatment from alcohol, in terms of their abstinence rates at 2 weeks post-discharge.

The secondary objectives are:To determine the efficacy of CBM training compared with sham training, in a population undergoing inpatient withdrawal treatment for AUD, in terms of their abstinence rates at 3, 6, and 12 months post-discharge.To determine whether the efficacy of CBM compared to sham training is moderated by the strength of approach bias at baseline.To determine whether the efficacy of CBM is moderated by risk-taking impulsivity.To determine whether participants who undergo CBM training will demonstrate a reduction in self-reported cue-evoked desire (wanting) for alcohol compared to those who undergo sham training.To determine whether those who receive CBM training impose a lower burden on healthcare services in terms of reduced use of emergency healthcare services and readmission to alcohol and other drug (AOD) withdrawal treatment services in the year following discharge, relative to those who receive sham training. These data will be used to estimate the cost savings to the healthcare system that would be associated with introducing CBM as a routine component of inpatient withdrawal treatment.

### Trial design

This is a randomised, double-blind, controlled, parallel-group trial. The protocol has been formulated in accordance with Good Clinical Practice, SPIRIT, and CONSORT 2013 guidelines.

### Study setting

Recruitment and data collection is taking place at three AOD residential withdrawal treatment units in the Melbourne metropolitan area in Australia.

### Sample size

Our recent pilot study indicated a difference in abstinence rates of 22% (i.e. 69% vs 47%) between the CBM and sham training groups. Using a smaller conjectured difference of 20% (e.g. 65% vs 45%) a two-sample, binomial test (two-sided α = 0.05) that utilises a pooled estimate of the variance, has 90% power to detect the conjectured difference when a total of 256 participants is randomised (i.e. 128 in each treatment arm). With an allowance for up to 15% drop out in the 2 weeks after discharge, based on an observed retention rate of 86% at 2 weeks in the pilot study, the target sample size was set at 300 (i.e. 150 randomised to each treatment arm). Recruitment is expected to take 22 months, given the throughput in the withdrawal treatment units, and the total study duration is likely to be 36 months.

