### Allocation

Site-specific randomisation sequences were generated by a researcher not involved in recruitment or data collection using a random number generator prior to beginning recruitment. A site-stratified 1:1 treatment arm allocation ratio is used, and is based on permuted blocks of variable size. The allocation sequence for each site is programmed into the training task on that site’s task laptop. When opening the training task, the researcher administering the training is prompted to enter the participant’s number, which then automatically causes the program to select the CBM or sham training, based on the pre-programmed randomisation sequence, such that the participant is allocated into a treatment arm ‘automatically’ – with no input from a researcher and without the researcher being able to predict a participant’s allocation prior to randomisation.

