### Primary outcome

In the ITT analysis of the primary outcome, the divisor for the proportion of abstinent participants in an arm will be the number randomized to that arm and individuals for whom alcohol use during the first 14 days post-discharge was not assessed, for any reason, will be deemed not to be abstinent. These proportions will be compared using a two-sample binomial test (two-sided α = 0.05) and a 95% confidence interval for the difference in the proportions will also be reported. The Cochran-Mantel-Haenszel test, stratified by site, will be conducted as a supportive analysis. In a further supportive analysis of the primary outcome, participants who complete fewer than four training sessions or who miss the 2-week assessment, will be excluded from the denominator (and the numerator) when the proportion of abstinent patients is calculated in each arm. This ‘per protocol’ analysis will use the same statistical methods as the ITT analysis.

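### The drop-out inflation preserves 90% power only if drop-outs leave the analysis; the planned ITT test counts them as non-abstinent, so its power with 300 participants is about 84% or about 94%, depending on an unstated denominator

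*Protocol article*

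**What the plan says.** The Sample size section specifies a "two-sample, binomial test (two-sided α = 0.05) that utilises a pooled estimate of the variance". It starts from the pilot's 69% vs 47% and moves to a more cautious effect: "Using a smaller conjectured difference of 20% (e.g. 65% vs 45"%). On that basis the test "has 90% power to detect the conjectured difference when a total of 256 participants is randomised (i.e. 128 in each treatment arm"). The drop-out step follows: "With an allowance for up to 15% drop out in the 2 weeks after discharge, based on an observed retention rate of 86"%. This pilot figure leads to the final size: "the target sample size was set at 300 (i.e. 150 randomised to each treatment arm").

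The Primary outcome section defines the test being powered. The divisor in each arm is the number randomised to it, and "individuals for whom alcohol use during the first 14 days post-discharge was not assessed, for any reason, will be deemed not to be abstinent". The Statistical methods section likewise includes all randomised patients whether or not they were followed up. Participants who miss the 2-week assessment are excluded only in a supportive per-protocol analysis, which also excludes anyone with fewer than four training sessions.

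The article does not say whether the pilot's 69% and 47%, or the design rates of 65% and 45%, are proportions of all randomised or of those assessed.

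**The concern.** Drop-out can affect a binary primary outcome in two ways. If the missing are removed, the rates stay as they are and the sample shrinks, so dividing by one minus the loss restores power. If the missing are counted as failures, the sample stays as it is, but both rates and their difference shrink by the proportion lost. Enlarging the sample by the usual factor then recovers only part of the power.

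The Sample size section treats drop-out in the first way and the Primary outcome section in the second. The 90% behind the choice of 300 is therefore not the power of the planned primary test at the allowed loss. On the less favourable reading, the type II error at 15% loss is about 16% rather than 10%, and a non-significant result would be read against a power figure that the ITT test does not have.

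**Working it through.** **Inputs.** From Sample size: two-sided α = 0.05, pooled-variance two-sample test, 65% vs 45%, 128 then 150 per arm, loss up to 15% (pilot retention 86%, so loss 14%). From Allocation: 1:1. From Primary outcome: divisor is all randomised, missing counts as not abstinent.

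**Formula.** With rates p1 and p2, mean rate p̄ and n per arm:

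power = Φ{ [ |p1 − p2| − 1.96·√(2p̄(1 − p̄)/n) ] / √([p1(1 − p1) + p2(1 − p2)]/n) }

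**Step 1: reproduce the plan.** For 65% vs 45% and n = 128, the null standard error is √(0.495/128) = 0.0622 and the alternative standard error is √(0.475/128) = 0.0609. Then (0.20 − 1.96 × 0.0622)/0.0609 = 1.282, and power is 90.0%. The required n is 127.9, i.e. 128 per arm, so the plan's figure reproduces. Inflation gives 256/0.85 = 301.2, rounded up to 302, against the stated 300; that gap is immaterial.

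**Step 2: what the inflation assumes.** 150 × 0.85 = 127.5 per arm. At 65% vs 45% this gives 89.9% power. The step therefore works for an analysis of assessed participants.

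**Step 3: the planned ITT test, with 65%/45% as rates among the assessed.** With a proportion d unassessed in each arm, the analysed rates are 0.65(1 − d) and 0.45(1 − d), and n stays at 150. At d = 0.15 they are 0.5525 and 0.3825, a difference of 0.17. The standard errors are √(0.4979/150) = 0.0576 and √(0.4834/150) = 0.0568. Then (0.17 − 1.96 × 0.0576)/0.0568 = 1.005, and power is 84.3%.

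| Loss in each arm | Analysed rates | Difference (points) | Power, 150 per arm |
|---|---|---|---|
| 5% | 61.75% vs 42.75% | 19.0 | 91.3% |
| 7% | 60.45% vs 41.85% | 18.6 | 90.1% |
| 8% | 59.8% vs 41.4% | 18.4 | 89.4% |
| 10% | 58.5% vs 40.5% | 18.0 | 88.0% |
| 14% (pilot) | 55.9% vs 38.7% | 17.2 | 85.1% |
| 15% (allowance) | 55.25% vs 38.25% | 17.0 | 84.3% |
| 20% | 52.0% vs 36.0% | 16.0 | 80.0% |

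Exact binomial enumeration of the pooled test gives 85.5% at 15% loss and 86.2% at 14%, about one point above the formula. Holding 90% by the formula would need 179 per arm (358 in total) at 15% loss, or 175 per arm (350) at 14%.

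**Step 4: the other reading.** If 65% and 45% already count the unassessed as non-abstinent, they apply directly to 150 per arm: (0.20 − 1.96 × 0.0574)/0.0563 = 1.553, and power is 94.0%. On this reading 128 per arm was already enough.

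**Step 5: sensitivity to unequal loss.** Losing 10% in the CBM arm and 20% in the sham arm takes the rejection probability to 97.7%; the reverse takes it to 51.5%. Equal loss is therefore a substantive assumption behind Step 3.

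**The case against.** The strongest reply is that the article states no power figure for 300. It attaches 90% to 256 participants at 65% vs 45%, and that sentence is correct. This stands as a matter of wording, but the only purpose of going from 256 to 300 is to keep that 90% in the face of drop-out, and under the planned missing-data rule it does not do so.

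Second, the direction of the error depends on a denominator that is not given. This stands in full. A reader might infer that the trial simply has 84% power and a 16% type II error. The documents do not support that as a flat statement. The inflation step favours rates among the assessed but does not prove it, the other reading gives more than 90%, 15% is an upper allowance, and equal loss is assumed.

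A reader might also try to settle the denominator from the pilot: "This study of 83 patients found a near-significant increase in rates of abstinence during the first 2 weeks following discharge". 86% of 83 is about 71, and 24/35 vs 17/36 reproduces 69% and 47% with p = 0.069 by an uncorrected chi-square. But all 83 can be split to fit as well:

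| Split of 83 | Uncorrected p | Yates p | Fisher p |
|---|---|---|---|
| 31/45 vs 18/38 | 0.047 | 0.078 | 0.073 |
| 34/49 vs 16/34 | 0.041 | 0.069 | 0.067 |
| 25/36 vs 22/47 | 0.039 | 0.066 | 0.047 |

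The article does not name the pilot's test, so a near-significant result fits either denominator.

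Nor does the dilution show that the 20-point assumption fails to be smaller than the pilot's effect. On one scale the comparison is 22 vs 20 points among the assessed, or about 19 (0.86 × 22 = 18.9) vs about 17 (0.86 × 20 = 17.2) counting missing as failure. The plan's description is right on both.

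Finally, the type I error is untouched and a 95% confidence interval for the difference is pre-specified, so a null result need not be judged by power alone. This stands and limits the severity.

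**Conclusion.** The sample-size step and the primary analysis treat drop-out in incompatible ways, and both are stated in the article, so this is not a detail left to the SAP. At the allowed loss, the planned ITT test with 300 participants does not have the 90% power that the calculation implies on either reading. The figure is about 84–85% at 14–15% loss if the design rates are among assessed participants and loss is equal in both arms, and about 94% if the rates already count missing as non-abstinent. About 90% describes only an analysis of assessed participants. No planned primary-outcome analysis is quite that, since the per-protocol set also requires four completed sessions.

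Severity is moderate. On the less favourable reading the shortfall is 5 to 6 points, and power stays above 80% at the allowed loss. The sample size remains defensible; the stated basis for it needs correcting.

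**What to change.** Keep 300 participants and the primary analysis as they are. In the sample-size text, or in the SAP before the primary outcome is analysed, state whether 65% and 45% are rates among assessed participants or rates with missing counted as non-abstinent, and give the matching power of the ITT test:

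- **Rates among the assessed:** about 84% at 15% loss and 85% at 14%, assuming equal loss in both arms, with a note that about 90% applies only to an analysis of assessed participants.
- **Rates with missing as non-abstinent:** about 94% with 150 per arm, with a note that the drop-out inflation was not needed for this test.

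The cost is one or two sentences, with no extra participants and no change of method. On the first reading the stated power becomes less favourable.
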